#### Utility of Different Communication Assessment Methods in Long-Term Prediction of Adjustment

Finally, to examine how communication measured early in the study predicts questionnaire measures of psychological and relationship adjustment at follow-up, we will estimate separate SEMs (again in an APIM framework), each of which uses a measure derived from each of the three different assessment methods (baseline questionnaire, EMA, and objective assessment) used in the study. First, we will estimate dyadic SEMs with actor and partner direct effects of early communication on each measure of adjustment at 12-month follow-up, adjusting for the person’s baseline assessment on the corresponding adjustment construct. In models based on questionnaire-measured communication, the general communication latent variable described above will be used. Objectively assessed communication, treated as a manifest variable, will be used in a parallel fashion in dyadic SEMs. Models based on EMA-measured communication will be estimated using two-level dyadic SEMs, with (the between-dyad variability in) repeated assessments of each patient’s and partner’s communication measure predicting psychological or relationship adjustment at follow-up, adjusting for the person’s baseline level on the outcome variable.

Analyses examining how f_0_ relates to psychological and relationship adjustment will include examination of how the trajectory of change in f_0_ over the course of the 15-min conversations predicts changes in psychological and relationship adjustment across the 1-year follow-up. First, trajectories of f_0_ across the conversation will be estimated for each partner by estimating a three-level (f_0_ for each talk turn nested within person nested within couple) multilevel growth curve model where f_0_ is regressed onto time (within conversation) and time^2^. Estimates will be generated for each person’s f_0_ intercept (i.e., initial f_0_ at the start of the conversation) and effect of time and time^2^ (linear and quadratic change, respectively, in f_0_ within the conversation). These values will be decomposed into within- and between-couple components. STATA will be used to analyze the primary models of interest in which longitudinal psychological and relationship adjustment separately are regressed on gender (as a covariate), role (patient vs. partner), f_0_ parameters within- and between-couple, wave (from baseline to 12 month), and their interactions. Model influence diagnostics and sensitivity analyses (including additional covariates) will be conducted to ensure stability of model results.

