The purpose of the present project is to provide a comprehensive and methodologically rigorous evaluation of both the SCP and RI models, including delineation of mediators (how they work) and moderators (for whom they work). Specific aims are: (1) To examine the overall fit of the SCP and RI models in explaining patient and partner psychological and relationship adjustment as they occur on a day-to-day basis and over the course of 1 year. (2) To examine the fit of the models for different subgroups: males vs. females, and patients vs. partners. (3) To examine the utility of the various methods of assessing communication (global self-report vs. EMA vs. objective measures) by examining the degree to which each of these baseline indices predicts self-reported psychological and relationship adjustment at 1-year follow up.

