We hypothesize that the SCP model will predict individual psychological adjustment *via* actor effects, and that the RI model will predict individual psychological adjustment *via* actor effects and relationship adjustment *via* both actor and partner effects (aim 1). It is also likely that the strength of these associations will vary between individuals or subgroups (aim 2). While there are numerous variables that could potentially moderate these mediating effects, based on the literature and potential clinical relevance, we chose to examine gender and role (patient vs. spouse). With regard to gender, stronger positive associations between perceived social constraints and distress have been found among male vs. female cancer patients (Zakowski et al., 2003). Further, females report discussing their cancer with a wider circle of confidantes than do males (Harrison et al., 1995) which could result in increased cognitive processing of their cancer experience outside the relationship. Thus, lack of cognitive processing may be a more important driver of distress for males vs. females. With regard to role, patients and partners often have different assumptions about how they should support each other, with some partners believing that it is harmful for the patient to discuss their cancer or any negative aspects of the situation (Peters-Golden, 1982); this is reflected in findings that partners report higher levels of protective buffering than do patients (Langer et al., 2009). Thus, it is possible that the negative effects of such buffering may be experienced more by patients than by partners, but this requires further examination. Regarding aim 3, because EMA and objective measures are less subject to reporting biases (e.g., social desirability and recall), we hypothesize that they will better predict outcomes.

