This study is the first comprehensive multi-method longitudinal study of couples’ communication in the context of cancer. The design incorporates key recommendations in the literature (Lepore and Revenson, 2007; Badr et al., 2013): (a) a dyadic approach that includes both partners and treats the couple as the unit of analysis; (b) the inclusion of dyads dealing with different types of cancer, including three cancers that affect both male and female patients so that role can be disentangled from gender; (c) the use of observational methods that enable analysis of interactional patterns and expressed emotional arousal as well as comparisons between these measures and self-report in predicting outcomes; (d) the use of EMAs that can capture the interactional nature of communication processes occurring day-to-day, and the temporal sequencing of communication behaviors, mediating variables and adjustment; and (e) assessment of communication using self-report questionnaires collected four times over the course of 1 year, affording analysis of change in communication patterns and mediators across time.

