### COVID Considerations

The first participants were enrolled in May of 2017. When in-person activities with human subjects were restricted due to the SARS-CoV-2 pandemic in March of 2020, we moved to IRB-approved remote enrollment. This allowed us to continue to carry out all study activities with the exception of the in-person couple conversation. The consent process was conducted *via* telephone and participants signed the consent form electronically through REDCap.

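### Aim 3 hypothesises that EMA and objective measures predict better than questionnaires, but the plan fits separate, unlike models and states no between-method estimate

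*Protocol article*

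**What the plan says.** The Introduction words Aim 3 as a contrast of methods: "To examine the utility of the various methods of assessing communication (global self-report vs. EMA vs. objective measures"), judged by how far each baseline index predicts self-reported adjustment at one year. The hypotheses paragraph gives the contrast a direction. Because EMA and objective measures are thought less open to reporting bias, "we hypothesize that they will better predict outcomes". The list of design features repeats the intention for the observational methods: "as well as comparisons between these measures and self-report in predicting outcomes".

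The analysis is in the section Utility of Different Communication Assessment Methods in Long-Term Prediction of Adjustment. There "we will estimate separate SEMs (again in an APIM framework), each of which uses a measure derived from each" of the three methods, adjusting for the person's baseline value of the outcome. The predictors enter as follows:

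- Questionnaire: "the general communication latent variable described above will be used". This is the factor with six proposed indicators from the Questionnaire Data section.
- Objective: "Objectively assessed communication, treated as a manifest variable, will be used in a parallel fashion in dyadic SEMs".
- EMA: "Models based on EMA-measured communication will be estimated using two-level dyadic SEMs, with (the between-dyad variability in) repeated assessments" of each member's communication.

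Fundamental frequency (f0), also an objective measure, has its own Stata model in the same section. It enters through growth-curve parameters, and the outcome is adjustment across all waves.

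On the move to remote enrolment in March 2020, COVID Considerations says: "This allowed us to continue to carry out all study activities with the exception of the in-person couple conversation".

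**The concern.** A hypothesis that one method predicts better than another needs an estimate of the difference between methods. The section gives none: no joint model, no difference in R-squared or in standardised coefficients, and no common analysis set. The fit benchmarks in the Overview (CFI, RMSEA, SRMR) measure how well a model reproduces its own covariances. They do not measure predictive value and cannot rank models of different structure.

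What remains is to read the separate results side by side. That reading would mix three things: true predictive value, how each model treats measurement error, and which dyads contribute. At stake is the interpretation of one of the three specific aims. Aims 1 and 2 are not affected.

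**Working it through.** **1. The plan's own figure.** The only power figure is 0.80 for indirect effects (Sample Size and Power): n = 264 complete dyads, r = 0.25 per path, R² = 0.15. Two-sided α = 0.05 is assumed, since it is not stated.

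- SE per path = √[(1 − 0.25²) / (264 × 0.85)] = √(0.9375 / 224.4) = 0.0646.
- Product test: z = 0.0625 / √(2 × 0.0625 × 0.0646²) = 2.73, so power = Φ(2.73 − 1.96) ≈ 0.78.

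This is close to the stated 0.80. It covers mediation only. The document gives no figure for Aim 3, so steps 3 to 5 are illustrations.

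**2. The models side by side.**

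| Method | Predictor | Measurement error | Dyads |
|---|---|---|---|
| Questionnaire | latent factor, six proposed scales | scale-specific error removed | all enrolled |
| EMA | between-dyad part of repeated reports | day-to-day variation separated out | all enrolled, subject to EMA response |
| Objective | manifest score | not removed | only dyads with a conversation |
| f0 | growth-curve parameters, Stata model | handled differently again; outcome over all waves | only dyads with a conversation |

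**3. Attenuation of a manifest score.** Observed validity = true validity × √reliability. The reliability of the objective score is not given, so 0.6 to 0.9 is assumed.

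| Reliability | True 0.20 shows | True 0.25 shows | Share of the true-score R² |
|---|---|---|---|
| 0.6 | 0.155 | 0.194 | 60% |
| 0.7 | 0.167 | 0.209 | 70% |
| 0.8 | 0.179 | 0.224 | 80% |
| 0.9 | 0.190 | 0.237 | 90% |

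If the questionnaire factor shows its full 0.20, the objective score falls short by 0.01 to 0.045 although the two are equally valid.

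**4. Effect on an informal ranking.** The simulation used 4,000 runs per setting, equal true validity of 0.25, true scores correlated 0.3, objective reliability 0.6 to 0.8, and 50% to 100% of 264 dyads with a conversation (all assumed). The questionnaire looked better in 60% to 77% of runs, where like-for-like measurement would give about half. The simulation takes the factor as free of error and omits the baseline adjustment, so it shows direction rather than exact size.

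**5. Precision of a like-for-like comparison.** This uses the Meng test for two correlations in the same sample: two-sided 0.05, 80% power, one correlation at 0.25, predictors correlated 0.1 to 0.5 (assumed), no baseline adjustment.

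| Dyads with all assessments | Detectable difference in r |
|---|---|
| 264 (100%) | 0.16 to 0.21 |
| 185 (70%, assumed) | 0.19 to 0.25 |
| 132 (50%, assumed) | 0.23 to 0.29 |

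The figure of 264 counts dyads complete at all four time points. Aim 3 needs questionnaire outcomes only at baseline and 12 months, so the available number may be somewhat larger.

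**The case against.** **The aim can be read as descriptive.** Separate models do answer how far each index predicts adjustment, and an article may leave the contrast to a full analysis plan. This stands in part. A reader might infer that the hypothesis will never be tested, but the document supports only that no comparison is stated here. The point survives because the article does more than stay silent: it fixes models with unequal error handling, and a contrast computed from their outputs would inherit that inequality.

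**The samples mostly coincide.** A reader might infer that all three methods use different cohorts. They do not: questionnaires and EMA continued under remote enrolment, so those two differ at most through EMA response. Only the objective measure is clearly affected. The article does not say how many dyads lack a conversation, nor that conversations never resumed, so the subset is mainly, not certainly wholly, pre-pandemic.

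**The bias is not shown for the whole hypothesis.** A reader might infer that the plan is tilted against EMA as well. The EMA model separates out day-to-day variation, though not stable reporting bias, and nothing in the document shows that it is disadvantaged against the questionnaire factor. The attenuation argument covers the manifest objective score only. It is also a simplification, because a factor across six different scales removes scale-specific variance that may itself predict the outcome.

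**The size is modest.** A gap of 0.01 to 0.045 is well below the differences that step 5 shows to be detectable. That is fair. Attenuation alone would not decide the result; it adds a directional error to a comparison that is already imprecise.

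**Conclusion.** The concern holds, as a should-fix. Aim 3 carries a directional, comparative hypothesis, while the stated analysis gives separate models with different error handling, a smaller subset for the objective measure, and no between-method estimate. A ranking read from those models would not be interpretable as a ranking of predictive value.

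On the illustration, an objective measure with true validity equal to the questionnaire factor's 0.20 would show 0.155 to 0.19. This rests on assumed reliabilities of 0.6 to 0.9 and on treating the factor as fully error-corrected. The direction for the objective measure follows from attenuation; the size is not fixed by the document. The share of dyads without a conversation is likewise unknown.

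**What to change.** 1. Define a common analysis set: dyads with questionnaire, EMA and conversation data.
2. For each outcome, pre-specify the comparison in that set as the difference between methods in R-squared gained over the baseline outcome, or in standardised effects. Give 95% intervals from a bootstrap that resamples dyads. The baseline-outcome adjustment is already planned and needs no change.
3. Name the objective index that enters the comparison, since behaviour codes, affect codes and f0 are all candidates.
4. Handle measurement error alike. One option is manifest scores for all three methods. The other is reliability correction for all three: Preliminary Analyses already plans reliability estimates for the questionnaire and EMA composites, and the roughly 30% of conversations rated by every coder (Observational Coding) can supply inter-rater reliability for a coded index. Using the five conversation segments as indicators would not be enough, because a rater's error can carry across segments.
5. Keep the separate full-sample SEMs as secondary, descriptive results.
6. A joint model with all methods may be added to show unique contribution, but it does not test which method predicts better.

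No new data are needed. The cost is some added modelling and a smaller, imprecise comparison. If the intervals are wide, Aim 3 should be reported as estimates rather than as a ranking.

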#### Supplemental Analyses

Analytic plans for the supplemental measures (bottom portion of Table 1) are described in turn below.

##### Stanford Brief Activity Survey

Descriptive statistics will be used to characterize patients and partners with regard to physical activity, an important health behavior known to ameliorate difficult effects of cancer treatment such as fatigue (Alfano et al., 2007).

##### Parenting Concerns Questionnaire

Data derived from this measure (posed only to participants who report having minor children in the home) will be used to examine associations between patient and partner parenting concerns and measures of communication, psychological distress, and relationship adjustment. This will build on findings from prior studies indicating that, among patients, parenting concerns are associated with higher levels of psychological distress (Park et al., 2016).

##### Functional Assessment of Chronic Illness Therapy—COST

This measure will be used to characterize the sample with regard to financial distress, both overall and as a function of sociodemographic and medical variables (cancer type and stage). We will also examine concordance or lack thereof in financial distress within couples and the trajectory of financial distress over time, from baseline to 1-year follow-up.

##### Coronavirus Impact Scale

This measure contains items designed to assess the extent to which the pandemic has caused change in multiple life domains: routines, family income/employment, food access, medical health care access, mental health treatment access, and access to extended family and non-family social supports. Additional items assess personal and family diagnoses of COVID, and perceived severity of pandemic-related stress and stress and discord in the family (none, mild, moderate, or severe). We will utilize descriptive statistics to characterize the sample with regard to COVID diagnoses and impacts on the life domains listed above. We will also conduct APIM analyses to examine concurrent intra- and inter-personal associations between pandemic-related stress and self-reported measures of communication (such as holding back) and well-being as measured by the FACT-GP.

##### Adult Attachment Scale

From the Revised Adult Attachment Scale, we will derive subscales of anxious and avoidant attachment styles for each participant. For analyses involving this measure, we will apply an Actor Partner Interdependence Mediation Model to APIM couples’ self-reported attachment, communication (disclosure and holding back), and physical well-being as measured by the FACT-GP. Indirect associations between a dyad member’s attachment (either anxious or avoidant) and their partner’s physical well-being are proposed as mediated by the dyad member’s own communicative behavior. We will examine model fit as described in the analytic overview above. Direct and indirect associations will be evaluated using 95% bootstrap confidence intervals.

## Discussion

To our knowledge, this is the first multi-method longitudinal study of couples’ communication in the context of cancer. Results will provide evidence to enable testing models of how couples’ communication is associated with adjustment to the cancer experience. Our long-term goal is to use these results to design and refine interventions that will improve couples’ communication and relationship functioning, alleviate cancer-related distress, reduce caregiver burden, and optimize patient and partner recovery from the rigors of cancer. Empirical support for the SCP model would indicate that interventions should focus on strategies that enhance cognitive processing. While these could include couple-based interventions that facilitate couples’ discussion of cancer-related issues, they may also include individual interventions that provide the opportunity for cognitive processing through disclosure to supportive others (e.g., a therapist or support group) or in non-social forms such as expressive writing. In contrast, support for the RI model would indicate that couple-based interventions are needed and should focus on enhancing intimacy through strategies to increase partners’ feelings of closeness and caring (e.g., increasing physical intimacy; engaging in meaningful activities together; disclosing personal, private thoughts and feelings and listening supportively to each other). Moderation analyses will examine whether these models may differentially apply depending on sex or role (patient or partner), or on the outcome targeted. Identifying differences in associations for these different subgroups will inform clinical application of the findings.

Use of technology in this study, specifically for EMA, will yield information regarding patients’ and partners’ smartphone access and their willingness to use the devices for research-based information and intervention delivery. Delivery of intervention content could occur using ecological momentary intervention or other types of real-time, mhealth methods.

Study limitations include a focus on patients with a subset of cancer diagnoses and the exclusion of patients either in the earliest stage of disease or facing death within 6 months. In addition, couples electing to participate may be unrepresentative of the larger group of patients with cancer and their spouses, as patients experiencing significant effects of disease or treatment might decline participation on that basis or for other reasons. Couples might also be hesitant to engage in the video-recorded conversation, or be reluctant to discuss topics related to cancer and its treatment, as these might result in emotional discomfort.

While the multi-modal nature of the assessments used in the study are a strength, as they provide multiple sources of information from both patient and partner, it is possible that some of the study procedures could be reactive and potentially affect responses to others. For example, engagement in the EMAs or the conversation could conceivably affect responses to other assessments by heightening perceptions or awareness of certain issues. We attempt to mitigate this in part by collecting the baseline self-report measures prior to the conversation and EMA. It is also possible that couples might discuss their responses to the EMA or other portions of the study, reducing the independence of their responses. We attempt to mitigate this by asking couples not to discuss their responses with each other. We believe this potential threat to internal validity is relatively low, and is offset by the benefits of collecting data in real time and in naturalistic settings.

## Dissemination Plans

Results will be published in scientific journals, presented at scientific conferences, and conveyed to a larger audience through infographics and social media outlets. We will also share findings with key stakeholders (oncology providers, patients and partners) to inform intervention planning and implementation.

## Ethics Statement

The studies involving human participants were reviewed and approved by the Arizona State University Institutional Review Board and Duke Health Institutional Review Board. The patients/participants provided their written informed consent to participate in this study. Reliance agreements were established to cover human subjects activities at the University of Washington and the Fred Hutchinson Cancer Research Center, with reliance on Arizona State University’s Institutional Review Board.
